#### Provisions for post-trial care {30}

There will be no provisions and no compensation to those who suffer harm from trial participation.

#### Outcomes {12}

Primary target variables:

Patient-related outcome measures (PROMs):Oswestry Disability Index (ODI)

Secondary target variables:Health questionnaire SF-36Pain intensity using the visual analog scale (VAS)Duration of the hospital stay (in days)Postoperative complicationsDuration of opioid useOperating time (in minutes)Re-admission within 3 weeks, 1 year, 2 years, 5 years postoperativelyBlood parameters for evaluating muscle damage:Creatine kinase (CK)Glomerular filtration rateMyoglobin (Mb)Erythrocyte sedimentation rateCreatine kinase: aspartate aminotransferase quotientProcalcitonin (PCT)C-reactive protein (CRP)White blood cell count (WBC)Interleukin (IL)-6

Renal parameters (e.g., creatinine clearance, glomerular filtration rate) will be measured to assess the influence of renal function on outcome measures, as creatinine kinase levels and myoglobin levels might be influenced by renal function. The severity of pain is determined using the visual analog scale (VAS). The scale is a 10-cm-long straight line, at the ends of which the extreme points of the pain to be measured are noted (0 cm = no pain, 10 cm = worst imaginable pain). The patient is asked to mark the intensity of his pain on the line with a pen [8].

The VAS is collected on the examination days before treatments (e.g., physiotherapy) are carried out. To assess the change in pain symptoms in the patients, the VAS values of the study groups at the time of the examination are compared and compared with statistical methods. The minimal clinically relevant reduction is given for input values above 30% [8].

The Oswestry Disability Index (ODI) is a questionnaire for evaluating functional disorders caused by back pain. The German version published in 2006 [9], the ODQ-D (Oswestry Disability Questionnaire- German), is scientifically recognized, and researchers regularly use it in back pain studies. The questionnaire is divided into 10 sections, each with 6 possible answers with point values of 0–5 points. The most appropriate answer should be ticked. As a result, the number of points achieved is set in relation to the maximum number of points and given as a percentage. Based on the results, the following judgments are made: 0–20% equals minimal, 21–40% equals moderate, 41–60% equals severe, 61–80% equals crippled, and 81–100% equals bed-bound or patients exaggerating their symptoms. The ODI will be measured as the primary outcome. The following time points will be assessed for the ODI: preoperatively, immediately postoperatively, 24 h, 48 h, 3 weeks, 1 year, 2 years, 3 years, and 5 years postoperatively (see also participant timeline {13}). The main outcome time point will be the 1-year evaluation. There is no repeated measure design statistical comparison planned and the 1-year, 2-year, 3-year, and 5-year outcome will be evaluated separately to evaluate the effectiveness of the respective treatment constantly for patients.

The SF-36 (Short Form Health 36) consists of 36 questions and is a general health questionnaire that uses 8 different dimensions to make statements about the patient’s state of health. It includes statements about the following: vitality, physical functioning, bodily pain, general health perceptions, the physical role of functioning, social role of functioning, and mental health.

#### Participant timeline {13}

The participant timeline is shown in Fig. 2.

#### Sample size {14}

The Institute for Medical Biometry and Statistics at the University of Freiburg, Germany, provided biometric advice. The sample size estimate of this confirmatory study (superiority study) is based on the primary target value “Oswestry Disability Index (ODI).” The ODI is the gold standard of patient-related outcome measures (PROMs) in patients after spinal surgery [9, 12].

Null hypothesis: H0: *T*-*S* = *δ*

Alternative hypothesis: Ha: *T*-*S* > *δ*

Test statistic: *Z* = (*d*-*δ*)/*sd*

*T*: full endoscopic therapy; *S*: microsurgical therapy (standard/control); *δ*: “clinically accepted limit of superiority”; *d*: true difference in the mean between the two groups; *sd*: standard error of *d*

Calculation of the sample size:$$N=2\times \frac{{\left({Z}_{1-\alpha }+{Z}_{1-\beta}\right)}^2}{\delta -{\delta}_0}\times {s}^2$$

*N* = number of cases per group; z1-α/1 − *β* = standard deviation for a one-sided 1-*α* or 1 − *β*; *δ* = true difference in the mean between the two groups; *δ*0 = clinically acceptable limit of the mean value difference (“relevance limit”); S2 = variance

With an expected difference *d* in the mean value between the two groups of *d* = 8 (maximum number of points 45 points in the ODI), an assumed standard deviation of *s* = 10, a clinically acceptable limit for the mean difference of *δ*0 = 4, a 5% level of significance (*α* = 0.05), an equivalent allocation to the groups (*k* = 1) and an assumed 10% drop-out rate, a number of cases of *n* = 87 per group, or a total of *n* = 174 is required to achieve a power of 80% (1 − *β* = 0.8).

#### Recruitment {15}

Recruitment will be performed at the Loretto Hospital Freiburg, Germany. Recruitment of the calculated sample size of patients will be feasible considering the high rate of spine surgeries at our hospital and our experience from the last 2 years. Our comprehensive cohort design further allows to include patients refusing to be randomized in a prospective parallel cohort, preventing selection bias. Additional strategies to increase recruitment include presenting the study on our hospital website, consultation of partner institutions, and providing information letters in the hospital's waiting rooms.

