### Trial design {8}

We will perform a comprehensive cohort trial involving a randomized and a prospective non-randomized study arm, each including intervention (full-endoscopic surgery) and control (microsurgical decompression) groups (superiority framework). Patients who do not consent to be randomized will be assigned to the non-randomized arm. Figure 1 illustrates the study design.

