#### Methods for additional analyses (e.g., subgroup analyses) {20b}

Not applicable as we do not plan to perform subgroup analyses yet.

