## Discussion

We present a protocol for a comprehensive cohort trial involving both a randomized and a non-randomized study arm to compare the full-endoscopic approach for the treatment of lumbar disc herniation against the gold standard, the microsurgical decompression technique. As far we are aware, this is the most comprehensive study to be performed on this topic. One main advantage is that our protocol involves one surgeon who is specialized in both techniques. This approach reduces confounding bias associated with different learning curves or multiple surgeons. Furthermore, we decided to focus on patient-reported outcome measures as these are of high clinical relevance. The Oswestry Disability Index is widely used in patients with back pain. The inclusion of this outcome as our primary outcome allows future meta-analyses to reliably compare our study with other relevant studies on this topic. A further advantage of our approach is that we included a non-randomized study arm which allows us to evaluate the impact of randomization on study outcomes. Although laboratory markers are surrogate markers and might fail to show clinical relevancy as diagnostic markers for muscle damage, interleukin 6 is considered as an important mediator that can reliably evaluate the impact of injury [13]. Modern endoscopes allow high-resolution visualization of a broad surgical field. However, some cases are judged to be not adequately treatable with the full-endoscopic procedure during surgery and require a switch (“conversion”) to the microsurgical technique during surgery. This can represent a problem if occurred too often, as the allocation will change during surgery. We aim to count these cases as complications for the full-endoscopic technique and analyze them as full-endoscopic patients, although the microsurgical method was finally applied. Nevertheless, based on our surgeons” experience, this occurred rarely in the last year, and we assume that not more than 2–3 patients in our cohort will be affected.

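### The preference cohort does not prevent selection bias; the plan should say that the 174 are randomised patients and how the self-selected cohort will be analysed

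*Protocol article*

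**What the plan says.** Trial design {8} sets up "a randomized and a prospective non-randomized study arm, each including intervention (full-endoscopic surgery) and control (microsurgical decompression) groups (superiority framework"), which makes four groups. Patients reach the non-randomised arm by refusing randomisation (Trial design {8}), by already preferring a technique (informed consent, {26a}), or by contacting the hospital to ask for one of the two methods (Eligibility criteria {10}, which lists these patients under exclusions and then assigns them to the matching non-randomised group).

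Sample size {14} states one hypothesis, full-endoscopic against microsurgical, with an expected difference "in the mean value between the two groups of *d* = 8" and "a clinically acceptable limit for the mean difference of *δ*0 = 4". It arrives at 87 per group and 174 in total. The word randomised does not appear in that calculation.

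Recruitment {15} first says that the calculated sample size is feasible and then adds: "Our comprehensive cohort design further allows to include patients refusing to be randomized in a prospective parallel cohort, preventing selection bias". Further measures to raise recruitment follow directly.

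The Abstract, the Background {6a} and the Discussion all say that the design lets the effect of randomisation be studied; in the Discussion, "we included a non-randomized study arm which allows us to evaluate the impact of randomization on study outcomes". Statistical methods {20a} lists repeated-measures ANOVA, paired t, Friedman and Wilcoxon tests, plus an exploratory univariate screening. The entry for additional analyses {20b} reads: "Not applicable as we do not plan to perform subgroup analyses yet".

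**The concern.** A cohort in which patients pick their own operation is where selection into treatment is strongest. Describing it as a protection against selection bias invites readers, and later the authors, to treat its treatment contrast as if it carried the weight of the randomised one. With only unadjusted methods listed, following the text would give a comparison that mixes the effect of technique with whatever led patients to choose it.

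The second issue is the population to which 174 applies. The recruitment target governs when enrolment ends, and Trial status puts recruitment between 14 January 2022 and 30 December 2025. A later analysis plan can define the analysis population, but it cannot change who was counted towards the target. If preference patients were counted, the randomised comparison would be smaller than planned.

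The third is a benefit claimed three times, the effect of randomisation, without a method directed at it.

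**Working it through.** **1. The plan's own figure.** Inputs from Sample size {14}: expected difference 8, margin 4, SD 10, one-sided α 0.05, power 0.80, 1:1 allocation, 10% drop-out.

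n per group = 2 × (1.645 + 0.842)² × 10² / (8 − 4)² = 77.3, so 78. Allowing for drop-out, 78 / 0.9 = 86.7, so 87 per group and 174 in total. This matches the plan exactly. (The formula as printed lacks the square on the denominator and would give about 309 per group before drop-out. The stated 87 comes from the squared form.) The number is right for one comparison of two groups.

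**2. Power if preference patients counted towards 174.** The protocol gives no randomised share, so the shares below are assumptions. Evaluable per group = 87 × share × 0.9. Power = Φ(4 / (10 × √(2/n)) − 1.645).

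| Share randomised | Evaluable per group | Power |
|---|---|---|
| 100% | 78.3 | 0.805 |
| 75% | 58.7 | 0.699 |
| 50% | 39.1 | 0.550 |
| 25% | 19.6 | 0.347 |

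**3. Confounding in the preference cohort.** The bias in an unadjusted difference from one baseline variable is roughly slope × imbalance. As an illustration only, a 5-point imbalance in preoperative ODI with a slope of 0.5 gives 5 × 0.5 = 2.5 points, against a margin of 4. Half that imbalance gives 1.25 points. Neither input is in the documents.

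**4. Precision of the effect of randomisation.** This is a difference of two treatment differences, with SE = 10 × √(4/m) for m evaluable patients in each of four cells. The difference detectable with 80% power at two-sided 5% is (1.960 + 0.842) × SE. Cohort sizes and the equal split are assumptions, and the two rows are alternative readings of 174 that cannot both hold.

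| Reading of 174 | m per cell | SE | Detectable difference | Power for 4 points |
|---|---|---|---|---|
| Randomised only, preference cohort of equal size added (348 in all) | 78.3 | 2.26 | 6.3 points | 0.425 |
| Both cohorts together, equal split | 39.15 | 3.20 | 9.0 points | 0.239 |

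The power loss in step 2 belongs with the second reading. Under the first there is none.

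**The case against.** Four stronger readings are tempting, and the document does not support them.

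*Four groups sized as two is an error.* It is not. In a comprehensive cohort design it is legitimate to size only the randomised comparison. The calculation assumes equal allocation, and 1:1 allocation exists only under randomisation (Sequence generation {16a}), since self-selected groups cannot be held to it. The natural reading is that the 174 are randomised. What stands is that no sentence says so, and that Recruitment {15} mentions the preference cohort next to the calculated sample size.

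*The arms will be pooled.* No section says this. The protocol calls them separate arms and a parallel cohort.

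*The plan rules out an analysis of the effect of randomisation.* The reason given under {20b} is confined to subgroups, a cohort contrast is a design-level comparison, and the effect of randomisation is absent from Objectives {7}. An ANOVA could carry treatment and cohort as factors, and a separate analysis plan may specify such a model. What stands is a mismatch between a benefit claimed three times and the tests listed. The ANOVA reply is also limited for the primary outcome, because Outcomes {12} excludes a repeated-measures comparison of ODI.

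*The bias sentence claims an unconfounded comparison in the preference arm.* It sits under Recruitment and may mean selection into the study. Even so, following refusers lets representativeness be assessed. It does not prevent selection, and the sentence draws no distinction from selection into treatment.

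Naming confounders is ordinary analysis-plan content, so the absence of a covariate list would not by itself be a finding. It matters here because it accompanies a claim that the bias is already prevented.

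**Conclusion.** The statement on selection bias is wrong as written and should be corrected. The preference cohort can inform how far the randomised results generalise, but its own treatment comparison is confounded by the way patients enter it.

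The sample size arithmetic is sound; only its population needs to be stated. The loss to about 70% or 55% power arises only if preference patients count towards 174, and it depends on assumed randomised shares of 75% and 50%. Nothing in the document shows that the confirmatory comparison is compromised.

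The effect of randomisation is a secondary claim without a matching method. On the protocol's SD of 10 it could be estimated only coarsely, with a detectable difference of about 6.3 points or about 9 points depending on the assumed cohort sizes. Both exceed the margin of 4.

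**What to change.** - In Sample size {14}, state that the 174 are randomised patients, that preference patients are additional, and that the confirmatory 1-year ODI test uses the randomised patients alone.
- In Statistical methods {20a}, analyse the preference cohort separately, adjusted at least for preoperative ODI and for other baseline prognostic variables already collected, such as preoperative VAS.
- Estimate the effect of randomisation as the treatment-by-cohort interaction in one adjusted model. Report it with its confidence interval, label it exploratory, and say that it will be imprecise.
- In Recruitment {15}, replace the final clause of the quoted sentence with a statement that the cohort allows the representativeness of the randomised patients to be assessed.

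The cost is one extra model, a few sentences and a more modest claim for the cohort. No clinical procedure or visit changes, and preoperative ODI is already recorded. If preference patients have in fact been counted towards 174 so far, the randomised target would take longer to reach.

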### Assignment of interventions: allocation

#### Sequence generation {16a}

Allocation (1:1) will be based on computer-generated randomization using a block size of 4 for sequence generation.

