#### Strategies to improve adherence to interventions {11c}

Our strategy to improve adherence to the follow-up monitoring includes a face-to-face adherence reminder session with the surgeon (FH) at the regular postoperative follow-up visits. Furthermore, we will ask patients during the visits how they can be best contacted (e.g., telephone, WhatsApp, SMS). The approach to remind patients to attend the follow-up visits for questionnaires will depend on their preferred way to be contacted.

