#### Concealment mechanism {16b}

Sequentially numbered, opaque, sealed envelopes (SNOSE) will be used to implement the allocation.

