#### Implementation {16c}

An independent researcher will perform the generation of the allocation sequence and preparation of the sealed envelopes. Allocation (1:1) will be based on computer-generated randomization using a block size of 4 for sequence generation. FH will enroll participants and screen for eligibility. Hereafter, envelopes will be handed over to GL by the independent researcher, who will assign participants according to the allocation sequence.

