#### Procedure for unblinding if needed {17b}

Not applicable as surgeons and patients will not be blinded.

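### A fixed, published block size of 4, with one unblinded surgeon who also screens, enrols and takes consent, can undermine allocation concealment in the randomised comparison

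*Protocol article*

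**What the plan says.** All references are to the protocol article.

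- **Sequence.** Sequence generation {16a}: allocation is 1:1 by "computer-generated randomization using a block size of 4 for sequence generation". Implementation {16c} repeats the same single block size. No stratification factor is stated.
- **Concealment.** Concealment mechanism {16b}: "Sequentially numbered, opaque, sealed envelopes (SNOSE) will be used to implement the allocation". Under Implementation {16c}, both the list and the envelopes come from a researcher described as independent. The envelopes are handed over after enrolment and screening, to a second team member.
- **Who controls entry.** Implementation {16c} names the person who "will enroll participants and screen for eligibility". The initials given there are those that Strategies to improve adherence {11c} attaches to the surgeon ("face-to-face adherence reminder session with the surgeon"). Informed consent {26a} lists the same person as one of two consent-takers; the other is the member to whom the envelopes are handed.
- **Who sees past allocations.** Background {6a} and Eligibility criteria {10} provide for one surgeon, and Study setting {9} for one hospital. Procedure for unblinding {17b} says that "surgeons and patients will not be blinded".
- **Route out of randomisation.** Trial design {8}: "Patients who do not consent to be randomized will be assigned to the non-randomized arm". Under Informed consent {26a} this option is presented to the patient in the consent talk.
- **Timing.** The article appeared in December 2022. Trial status gives recruitment from January 2022 to a planned end in December 2025.

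**The concern.** In a 1:1 block of 4, once two patients have gone to one arm the rest of the block is determined. Someone who knows the block size and the earlier allocations can work out some assignments before the envelope is opened, however well it is sealed. Here the person best placed to know the earlier allocations, because he or she performs every operation unblinded, is also the person who judges eligibility and talks to the patient about consent.

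Two features enlarge the opportunity. Several exclusions in Eligibility criteria {10} call for judgement, such as massive sequestration, other serious disease and other severe spinal disorders. A patient who declines randomisation is not lost to the study but moves to the parallel cohort, so a changed decision leaves little trace. Recruitment {15} says that the cohort design prevents selection bias. With predictable allocation, the same design offers selection a route.

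At stake is the comparability of the two randomised groups, on which the causal reading of the confirmatory ODI comparison depends.

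**Working it through.** **Inputs.** Block size 4 and ratio 1:1 (Sequence generation {16a}); total 174, expected difference 8, relevance limit 4, SD 10, one-sided alpha 0.05, power 80%, drop-out 10% (Sample size {14}).

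**The plan's own figure.** The article gives no predictability figure, so 174 serves only to turn a share into a count. It reproduces with the difference squared: 2 × (1.645 + 0.842)² × 10² / (8 − 4)² = 77.3, so 78; 78 / 0.9 = 86.7, so 87 per group and 174 in total. The section does not divide 174 between the randomised and non-randomised parts. I take it as the randomised total.

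**Certain allocations, all earlier ones in the block known.** There are 6 equally likely orderings of two E (endoscopic) and two M (microsurgical).
- EEMM and MMEE: positions 3 and 4 are certain (2 each).
- The other four: only position 4 is certain (1 each).
- Expected per block: (2 × 2 + 4 × 1) / 6 = 4/3, which is 1/3 of 4 positions, or 33.3%. In a single block it is 25% or 50%.
- 174 patients are 43 full blocks plus 2. The two extra patients sit in positions 1 and 2, which are never certain. 43 × 4/3 = 57.3, so about 57 (33.0%), with SD √(43 × 2/9) = 3.1.

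**Best guess (the arm used less so far in the block).** By position: 1/2, 2/3, 2/3, 1. Mean = 17/24 = 70.8%, against 50% with no information.

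**If knowledge lags.** The article does not say how soon the surgeon learns each allocation, or how far enrolments overlap.

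| Known at the next enrolment | Certain in advance | Best guess correct |
|---|---|---|
| All earlier allocations in the block | 4/12 = 33.3% | 17/24 = 70.8% |
| All but the latest | 1/12 = 8.3% | (1/2 + 1/2 + 2/3 + 2/3) / 4 = 58.3% |
| All but the last two | 0% | (1/2 + 1/2 + 1/2 + 2/3) / 4 = 54.2% |

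**What it could do to the result (illustration only).** The prognostic gap is an assumption, not a figure from the article. Suppose patients entered when endoscopy is certain would, on the same treatment, score 2 to 5 ODI points better than those entered when microsurgery is certain. The bias is the certain share times that gap.
- At 1/3: 0.7 to 1.7 points. With 78 evaluable per group, the standard error is 10 × √(2/78) = 1.60, and the one-sided type I error rises from 5% to about 11% to 27%.
- At 1/12: 0.2 to 0.4 points, and about 6% to 8%.
- At 0%, or with no selection: no bias from certain allocations.

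**Effect of varied block sizes.** Simulated for 174 patients, for a guesser who sees every past allocation and knows the possible sizes but not the block boundaries.

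| Scheme | Certain in advance | Best guess correct |
|---|---|---|
| Fixed 4 | 33% | 71% |
| Random 4 or 6 | 5% | 69% |
| Random 4, 6 or 8 | 2% | 68% |

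A larger block that stays fixed and known helps less: 25% certain at size 6 and 20% at size 8.

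**The case against.** The case on the other side has four parts.

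**Concealment is already provided for.** An independent researcher generates the sequence, prepares the envelopes and releases them only after enrolment. This stands: it prevents anyone seeing the next envelope early. It does not prevent deduction from earlier allocations, which needs no access to the envelope. The sentence on who then assigns can be read as the second team member or the independent researcher. The point holds on either reading, because the surgeon enrols and learns past allocations in both.

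**One third is a maximum.** A reader might infer that the surgeon will know a third of allocations outright. The article does not support that as a flat statement: it holds only if every earlier allocation in the block is known when the next patient is enrolled. A second person does the assigning, and enrolments may overlap. The supported range is 0% to 33%. Nothing in the text requires a delay that would keep the figure low.

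**The exit belongs to the patient.** A reader might infer that the surgeon can move patients out of randomisation, or that concealment fails. The article says neither. The non-randomised arm depends on the patient's refusal or prior preference, and no section gives the surgeon discretion to reassign. What remains is influence through eligibility judgements and the consent talk. That is an opportunity, with no evidence of use.

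**Varied blocks leave most of the guessing in place.** This also stands: the best-guess rate moves only from 71% to about 68%. What falls materially is certainty.

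**Conclusion.** The point holds as a weakness in a rule the article states, not as an omission. A single fixed and published block size, combined with one unblinded surgeon who screens, enrols, shares in taking consent and operates, can undermine allocation concealment.

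The size is up to 33% of allocations certain in advance, about 57 of 174, with a best guess right 71% of the time. This rests on two assumptions: all earlier allocations in the block are known at each enrolment, and 174 is the randomised total. The share does not depend on the second. Publication adds certainty, but this team could work with the block size even had it not been published. Any bias in the ODI comparison would further require that the knowledge be acted on, which the documents do not show. The change is worth making because it is cheap and protects the part of the study that carries the confirmatory claim.

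**What to change.** 1. At the next block boundary, have the independent researcher regenerate the unopened remainder of the list with randomly varied block sizes (for example 4, 6 and 8). Do not disclose the sizes to the surgeon or the consent-takers. The amendment and registry entry can say that sizes vary and withhold them until recruitment ends.
2. State in Implementation {16c} that the independent researcher, not a consent-taker, opens each envelope, and only after eligibility, consent and the choice to be randomised have been logged with date and time. Release after enrolment is already the stated order; naming who opens the envelope and keeping the log are new. The log makes late changes to the non-randomised arm visible.

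**Gain.** Certain allocations fall from up to 33% to about 2%. The best-guess rate stays near 68%, so guessing is not removed.

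**Cost.** New envelopes for the remaining patients and a protocol amendment, using a researcher already in place. Final imbalance could reach 4 patients instead of 2, or 6 if the switch is made mid-block, because an existing imbalance of 2 would carry over. No treatment, visit or endpoint changes. The benefit depends on how many envelopes remain unopened, which the article does not show; recruitment was planned to end in December 2025.
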